**Enrolment** **Week 8 Week 20 Week 24**

Time zero (End of intensive phase) (End of continuation phase)

(follow up period starts )

**Week 36 Week 48 Week72 Week 96**

(End of trial)

| Study procedures | Screening | Enrolment  Study Drug  T=0h | Week 8  (end of intensive phase) | Week  20 | Week 24  (end of continuation phase) | (Weeks 36,48,72 and 96) |
| --- | --- | --- | --- | --- | --- | --- |
| Medical History | X |  |  |  |  |  |
| Physical Examination | X |  | X | X | X | X |
| Sputum for AFB smear | X |  | X | X | X | X |
| Sputum for culture |  | X | X | Xa | X | Xa |
| Sensitivity testing |  |  |  | Xb |  |  |
| Informed consent | X |  |  |  |  |  |
| Haematology and Clinical chemistry | X | X | X | X | X | X |
| Urine analysis | X | X |  |  |  |  |
| Pregnancy test | X |  |  |  |  |  |
| HIV testing  CD4 test | X  Xd |  |  |  | Xd | Xd |
| Randomisation |  | X |  |  |  |  |
| Drug administration |  | X | X | X | Xe |  |
| Adverse Events |  | Symptom checklist | X | X | X | X |

Xa It the sputum smear is positive

Xb Sensitivity testing of screening smear and 5 month smear if sputum is positive.

Xd CD4 testing only for HIV positive TB patients. Repeat CD4 test on weeks 24, 48, 72 and 96. Not indicated at week 36.

Xe By the end of week 24, treatment should be completed.

Patients will be instructed to attend the TB treatment centre, for the duration of treatment; both the intensive and maintenance phases. All drug doses will be administered under observation and documented by the trial nurse. All drug doses in the continuation phase will be administered under standard operation of DOTS of the country. Patients will also be evaluated for clinical, haematological and biochemical parameters during these follow up period.

Trial subjects will be followed up for 72 weeks after the completion of treatment. They will be required to come to TB treatment centre for clinical, haematological and biochemical assessments at the end of 36 weeks ,48 weeks ,72 weeks and 96 weeks after initiation of treatment. A home visitor will trace individuals who fail to come at the specified time points. At each follow-up time, subjects will provide three sputum samples: one spot, one morning and a second spot sputum specimens for smear examination at each of the three follow up visits. Cultures will be done only for smear positive individuals (as defined above).

## 3.8 Special considerations relating to patient counselling and HIV testing

All eligible patients will be informed about the relationship between HIV-infection and TB by the examining physician. The advantages of testing and knowledge about status to the patient and family will be explained. Health education will be given to the patient on the need to prevent and treat opportunistic infections, if HIV co-infected. Patients who agree to consider testing will be advised to visit a trained HIV-counsellor in the same institution. The nurse will discuss the pros and cons of testing with the patient. The patient will be encouraged to ask questions including on the confidentiality of the procedures of testing. Those patients who agree to be tested will be provided with a request form for the laboratory. The patient will meet and discuss the result with the Counsellor who will continue advising the subject over the next months as required. HIV-negative subjects will also be encouraged to have appointments with the counsellor to discuss safe practices. The counsellor will be responsible for providing information to the HIV-positive subject on available support for sero-positive individuals. The Counsellor will keep confidential written records of the discussions.

## 3.9 Special considerations relating to HIV patient management

In the interests of good patient management, HIV testing will be done as part of pre-study assessment. HIV positive patients have higher rates of recurrent disease compared to HIV negative patients. Pre- and post counselling is done routinely under national guidelines at the TB centre. Subjects found to be HIV-positive will be referred to the physician responsible for HIV-related care at the site and those with CD4 count below 220 in Nigeria and those with CD4 below 351 in Ethiopia will be excluded from this study. All enrolled HIV positive patients (i.e. patients with CD4≥220 in Nigeria and CD4>350 in ethiopia) will have follow up CD4 test at weeks 24, 48, 72 and 96. Those patients with CD4 below 200 in Nigeria and CD4 below 351 in Ethiopia during the follow up period will be referred to the physician responsible for HIV-related care including ART. Treatment of HIV positive patients in Ethiopia and Nigeria is as follows:

If anti-retroviral therapy is indicated, patients will be referred for treatment so that they can benefit from the highest possible local standard of care for HIV infection. Prophylaxis with co-trimoxazole may be recommended by the patient's physician and any medications prescribed will be documented on the CRF.

Nigeria apply the WHO guidelines for scaling up antiretroviral access in resource-limited settings, ie antiretroviral treatment should be initiated in TB patients if there is a very high risk of HIV disease progression and mortality. These would occur mainly among TB patients with CD4 T cell count <200 cells/mm3. However, in Ethiopia HIV infected patients with CD4 T cell count<351 are initiated on antiretroviral treatment (Guidelines for management of opportunistic infections and Anti retroviral treatment in adolescents and adults in Ethiopia, federal HIV/AIDS prevention and control office, FMOH, July 2007).

Those patients who are eligible for ART will be referred to the St Peter's Hospital and Bole Health center in Ethiopia and Ebonyi State University Teaching Hospital and ABA South LGA Hospital in Nigeria. Both hospitals are collaborating centres in the trial. Those patients who are eligible for ART-( excluded from this study) will be referred and treated at centres where ART treatment is provided based on the National guidelines in both countries.

# 4. STATISTICAL CONSIDERATIONS

The objective of the study is to demonstrate that FDCs have equivalent efficacy to the loose formulations.

Sample sizes of 498 from the intervention group and 498 from the standard group achieve 90%

power at a 5% significance level using a one-sided equivalence test of proportions when the

proportion of patients cured in the comparator group (Ps) is 96% and the maximum allowable difference (clinically acceptable difference) between proportions in the two treatment groups that still results in equivalence (the range of equivalence) is 4%. A sample size of 498 in each group is estimated with dropout rates of 10%. Two study sites will conduct the trial and contribute to the total sample size. Ethiopia will contribute a total of 498 subjects (249 in each arm) per country to reach the sample size of 996.

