## 6.4 Data analysis

The database file generated thus will be converted into statistical package STATA software version 7 (STATA Corporation, Texas, USA) and analysed by the study statistician, and PI in collaboration with the study director. Analysis will be both (a) by intention-to-treat, and (b) per protocol (excluding those who did not receive adequate chemotherapy or were withdrawn from the study), including survival analysis.Subjects will be compared based on their assigned treatment using chi-square, Student's t-test or the Wilcoxon rank sum test as appropriate depending on the scale of measurement and the validity of underlying assumptions for the baseline characteristics. Primary and secondary outcomes for each study subject will be recorded as positive (desirable) and negative (not desirable) at a pre-specified time. For primary outcome Chi-square will be used to compare proportions of culture positive and culture negative subjects at the end of the study in the two treatment groups. The effects of confounding variables (such as age and sex) will be adjusted using multiple logistic regression. In model construction, backward elimination will be employed using important independent variables initially. An alpha of 0.10 will set the significance level for entering a variable into the model. Chi-square will also be used to compare differences in each of the three secondary end points. In the whole analysis, an alpha of 0.05 will set the significance level for testing the null hypothesis. In presenting results exact p-value as obtained from the computer program will be presented.

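### Section 4 sets equivalence within 4 points as the objective, but its 90% power belongs to a one-bound test that supports only non-inferiority

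*Protocol*

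**What the plan says.** All the design figures are in Protocol section 4. The aim is given as: "The objective of the study is to demonstrate that FDCs have equivalent efficacy to the loose formulations". The power statement opens with "Sample sizes of 498 from the intervention group and 498 from the standard group achieve 90" (per cent), and the test behind that figure is described in these words: "power at a 5% significance level using a one-sided equivalence test of proportions when the" (the assumptions follow). The assumed comparator cure rate is stated as "proportion of patients cured in the comparator group (Ps) is 96" per cent. The largest acceptable difference between the arms, "that still results in equivalence (the range of equivalence) is 4" per cent, is given without a direction. On losses, "A sample size of 498 in each group is estimated with dropout rates of 10" per cent.

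Section 6.4 names the primary analysis: "For primary outcome Chi-square will be used to compare proportions of culture positive and culture negative subjects at the end of the study". It mentions no margin. The same section plans both an intention-to-treat and a per-protocol analysis. Section 3.2 (Study withdrawals) keeps withdrawn and lost patients in the intention-to-treat set. The term non-inferiority does not appear in the protocol.

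**The concern.** Equivalence and non-inferiority are different claims. Equivalence within 4 points means concluding that the true difference lies between −4 and +4, so both bounds must be rejected. Non-inferiority means concluding only that the fixed-dose arm is not worse by 4 points or more, so one bound suffices. Section 4 uses equivalence wording for the objective, the test and the margin, but calls the powered test one-sided.

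This affects what the report may conclude. If it claims equivalence by testing both bounds, the chance of success is below the stated 90%. If it tests only the lower bound, the 90% is right but the word equivalent is not earned. Section 6.4 does not settle which is meant, because a chi-square test of difference uses neither bound.

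**Working it through.** **Inputs.** From section 4: comparator cure 96%, margin 4 points, one-sided 5%, power 90%, 498 per arm, 10% dropout. The intervention cure rate is not stated. I assume 96%, so the true difference is zero.

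**Step 1: reproduce 498.** For a test of one bound,

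n = [(z₀.₉₅·σ₀ + z₀.₉₀·σ₁) / 0.04]²

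- σ₁² = 2 × 0.96 × 0.04 = 0.0768, so σ₁ = 0.2771.
- For the score (Farrington-Manning) test, the restricted null rates are 0.9320 and 0.9720. Then σ₀² = 0.9320 × 0.0680 + 0.9720 × 0.0280 = 0.0906, so σ₀ = 0.3009.
- n = [(1.645 × 0.3009 + 1.282 × 0.2771) / 0.04]², which gives 452 per arm.
- 452 × 1.10 = 497.2, rounded up to **498**, the stated figure. Dividing by 0.9 instead gives 503.

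The unpooled (Wald) version has σ₀ = σ₁ and gives 412, or 454–458 after dropout, which does not match. The score calculation against one margin matches exactly.

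**Step 2: could a two-bound calculation give 498?** With a true difference of zero and equal arms, the approximate power for both bounds is

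2·Φ[(0.04 − z₀.₉₅·σ₀/√n) / (σ₁/√n)] − 1

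For 90% this needs 520 (Wald) to 566 (score) evaluable per arm, or 578 to 629 per arm after dividing by 0.9. The smallest of these exceeds 498 even before dropout. At 452 per arm the score version gives 2 × 0.9002 − 1 = 80.0%.

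**Step 3: power at the planned size.** Exact binomial enumeration, 96% in both arms, 5% per side. With 10% lost, 498 × 0.9 = 448 remain evaluable.

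| Analysed per arm | One bound, score | One bound, Wald | Both bounds, score | Both bounds, Wald |
| --- | --- | --- | --- | --- |
| 448 | 90.3% | 92.0% | 80.7% | 83.9% |
| 498 | 93.1% | 93.9% | 86.1% | 87.8% |

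Against 90%, the two-bound shortfall is about 6–9 points at 448 (90 − 83.9 = 6.1; 90 − 80.7 = 9.3) and 2–4 points at 498 (90 − 87.8 = 2.2; 90 − 86.1 = 3.9).

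**Step 4: why the second bound costs power.** With equal arms and equal true rates the two tests are mirror images. At 448 per arm (score) each passes with probability 0.9033 and fails with probability 0.0967. The two failures do not overlap here, so power for both is 1 − 2 × 0.0967 = 0.807.

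**The case against.** The best defence is that section 4 openly says one-sided. It discloses the test, the alpha, the control rate and the margin, and its sample size reproduces exactly. A reader might infer from the two-bound figures that the sample size is miscalculated or the trial too small. The documents do not support that: for a one-bound test, 498 per arm is enough. Nor does the protocol claim 90% power for a two-bound test in so many words. The rationale also fits a one-directional design: the bioavailability concern in section 2.1 is that fixed-dose products may do worse. This part of the objection stands, and it makes the defect a mismatch between claim and test.

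A second objection is that 81–84% applies only if a tenth of each arm is lost from the analysis, whereas section 3.2 keeps such patients in the intention-to-treat set. That also stands. It would be wrong to quote 81–84% as the power at 498 per arm; the figure fits a per-protocol set. With all 498 analysed the range is 86–88%, still below 90%.

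A third is that the upper bound is empty, because 96% plus 4 points is 100%. This fails. The true difference cannot exceed +4 at that control rate, but the test uses the observed difference and its standard error, and step 4 shows that it fails as often as the lower one.

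Finally, section 6.5 defers the analytical plan, which may state a one-bound criterion. It would still have to depart from the objective in section 4 and the chi-square test in section 6.4.

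**Conclusion.** The point holds as a mismatch between the stated claim and the powered test. The 90% in section 4 is the power to show non-inferiority with a 4-point margin. For equivalence within 4 points, the same design has about 81–84% power with 448 evaluable per arm and about 86–88% with all 498 analysed.

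These figures assume 96% cure in both arms, because the intervention rate is not given. With the comparator at 96%, a true difference in either direction lowers the chance of passing one of the bounds. The 86–88% also assumes that 96% holds across everyone analysed. If losses were scored as not cured, the expected rate would be nearer 0.90 × 0.96 = 86.4% and the figure would not apply. No additional patients are needed to resolve the mismatch.

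**What to change.** In section 4, restate the objective and the intended conclusion as non-inferiority: shown when the lower limit of the one-sided 95% confidence interval for the cure rate difference, fixed-dose minus loose, lies above −4 points. Use non-inferiority in place of the equivalence wording for the test and the margin. The 498 per arm and 90% power then stand.

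Change section 6.4 as well. The chi-square test named there tests for a difference and uses no margin, so correcting section 4 alone would leave the primary analysis unable to answer the restated question. The primary analysis should apply the same confidence-limit rule.

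If the sponsor prefers to keep equivalence, require both bounds, −4 and +4 points, in both sections. Restate the power as about 81–84% with 448 evaluable per arm, or 86–88% with 498 analysed per arm, together with the assumed intervention rate.

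Either route is a change of wording that adds no patients. The price is a narrower claim in the first case and a less favourable stated power in the second.

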# 5. ASSESSMENT OF SAFETY & TOLERABILITY

**5.1 ADVERSE EVENTS**

Safety will be assessed by monitoring the occurrence of adverse events. An adverse event is a symptom, sign, clinical illness, or an abnormal laboratory result that was either: (i) not present on Day 0 but occurred during follow-up, or (ii) was present on Day 0 but has since become worse. There will be a checklist of symptoms and signs that will be sought at each assessment (see CRF). Routine laboratory tests (detailed in the CRF) will be done at baseline and repeated only as clinically indicated during follow-up. Other laboratory tests will done if clinically indicated.

**All adverse events will be graded as: 0=normal, 1=mild, 2=moderate, 3=severe** according to ICH Clinical Safety Data Reporting. An assessment of the cause of the adverse event will be done by the clinicians. The relationship to study drug will be graded as (i) none, (ii) unlikely, (iii) possible, (iv) probable, (v) definite, (vi) unknown. Refer to the WHO/TDR SOP for these definitions. Adverse events will be treated on their merits and patients followed up as necessary. All adverse events will be recorded in the CRF. All serious and unexpected adverse events, as defined in the SOPs, will be recorded in the SAE form (see below). Necessary details will include: (i) the description of adverse event, (ii) onset date, (iii) speed of inset: sudden, gradual, unknown, (iii) duration, (iv) severity, (v) relationship to study drugs, (vi) outcome, (vii) measures taken (symptomatic treatment, discontinuation of treatment).

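### Section 5.1 makes repeat routine laboratory tests conditional on clinical indication, while the visit schedule requires haematology and clinical chemistry for every patient at every visit

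*Protocol*

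**What the plan says.** The protocol gives two instructions on blood testing after baseline.

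- **Section 5.1 (Adverse events):** "Routine laboratory tests (detailed in the CRF) will be done at baseline and repeated only as clinically indicated during follow-up". The next sentence makes any other laboratory test conditional on clinical indication as well.
- **Section 3.6 (schedule table):** the row reads "Haematology and Clinical chemistry | X | X | X | X | X | X". The six columns are screening, enrolment, week 8, week 20, week 24, and one column for weeks 36, 48, 72 and 96.
- **Section 3.6 (text on the post-treatment period):** "They will be required to come to TB treatment centre for clinical, haematological and biochemical assessments at the end of 36 weeks", and likewise at weeks 48, 72 and 96.
- **Section 3.6 (text on attendance during treatment):** the paragraph covers attendance "for the duration of treatment; both the intensive and maintenance phases" and ends: "Patients will also be evaluated for clinical, haematological and biochemical parameters during these follow up period".

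Section 5.1 counts an abnormal laboratory result as an adverse event. Section 2.2 lists the proportion of patients with any adverse event during chemotherapy as a secondary outcome.

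**The concern.** One section tells the site to take bloods at fixed visits from everyone; the other tells it to take them only when there is a clinical reason. Nothing in the protocol says which prevails.

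What is at stake is how laboratory adverse events are found. Under the schedule, a silent rise in liver enzymes at week 8 would be detected and counted. Under section 5.1, if follow-up there includes treatment, it would be detected only if something prompted a test. With two countries enrolling, ascertainment of the outcome could depend on which section a site happens to follow. Safety is part of the general objective in section 2.2, and section 2.1 says that no safety data exist for the four-drug combination, so this is not a peripheral measurement.

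**Working it through.** No stated figure has to be reproduced. The check sets the two instructions side by side and counts panels.

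**Do both instructions concern the same tests?** Section 5.1 refers to the CRF for its routine set, and the CRF is not shown. Section 3.6 lists full blood count, liver function and renal function in the initial assessment, which it also refers to the CRF. That makes the identity probable. If these tests were not the routine ones, they would fall under the next sentence of section 5.1, which is also conditional. Section 5.1 makes them conditional either way.

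**Is the schedule row conditional?** The table footnotes its conditional tests: culture (a), sensitivity testing (b) and CD4 (d). The haematology and chemistry row carries no footnote.

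**What does follow-up mean in section 5.1?**

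- *Narrower (after treatment).* The time line in section 3.6 places "follow up period starts" at the end of treatment. The text adds: "Trial subjects will be followed up for 72 weeks after the completion of treatment". The relapse outcome in section 2.2 uses the term in the same way.
- *Wider (after Day 0).* Section 5.1 defines a new adverse event as one "not present on Day 0 but occurred during follow-up". If that meant only after treatment, a new event during chemotherapy would not meet this clause, and the secondary outcome would lose its new-onset events. The same word a few sentences later most naturally has the same meaning. The treatment attendance paragraph in section 3.6 also ends by calling the period follow-up.

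**Unprompted panels per patient after baseline**

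| Period | Schedule | Section 5.1, wider | Section 5.1, narrower |
| --- | --- | --- | --- |
| Weeks 8, 20, 24 | 3 | 0 | 3 |
| Weeks 36, 48, 72, 96 | 4 | 0 | 0 |
| Total | 7 | 0 | 3 |

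**Upper bounds over the 996 planned patients (section 4), ignoring dropout**

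- On treatment: 996 × 3 = 2,988 panels, in conflict on the wider reading only.
- After treatment: 996 × 4 = 3,984 panels, in conflict on either reading.
- Together: 2,988 + 3,984 = 6,972 panels.

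The table places week 24 in the treatment period. If week 24 is instead taken as the first follow-up visit, the split is 2 + 5: 996 × 2 = 1,992 and 996 × 5 = 4,980, with the same total.

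**Outcomes affected.** Section 2.2 lists eight secondary outcomes. On the wider reading one is affected, any adverse event during chemotherapy. On the narrower reading none is, provided week 24 belongs to treatment.

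**Tests outside the conflict.** Urine analysis is scheduled only at screening and enrolment, and the pregnancy test only at screening. For these, section 5.1 and the schedule agree.

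**The case against.** The strongest reply is that the firm part does little harm and the harmful part is not firm. The conflict at weeks 36 to 96 is clear, but those panels cannot change an outcome confined to chemotherapy. The effect on that outcome needs the wider reading, and three places in the protocol use follow-up for the post-treatment period. The closing sentence of the treatment attendance paragraph is itself ambiguous, since the post-treatment paragraph comes straight after it. In practice, staff working from the visit table would probably draw the bloods, so the panel totals overstate the likely loss. The week 24 boundary is also open, since section 3.9 lists it among the CD4 follow-up times. Finally, aligning section 5.1 with the table assumes that the table reflects the intended plan.

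Much of this stands as a limit on size. The on-treatment part is likely, not certain. The totals are upper bounds, not forecasts. If week 24 opens follow-up, the narrower reading loses one on-treatment panel too, and it is then no longer clear that no secondary outcome changes. None of it reconciles the two instructions. On intent, the table and two sentences in section 3.6 all point to scheduled testing, against one sentence in section 5.1.

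**Conclusion.** The inconsistency is real. It is certain for weeks 36, 48, 72 and 96 (4 scheduled panels per patient against 0) and likely for weeks 8, 20 and 24 (3 against 0). This assumes that the routine tests in section 5.1 include the blood count, liver and renal tests, or else that its sentence on other tests covers them. The on-treatment part further assumes that follow-up in section 5.1 starts at Day 0.

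The consequence is moderate. On the wider reading, one of eight secondary outcomes is under-ascertained. Only abnormalities with neither symptoms nor signs are missed, because the symptom checklist and the physical examinations at weeks 8, 20 and 24 can still prompt a test. The change in the proportion cannot be derived from the protocol. The primary endpoint is unaffected, the serious adverse event outcome is little affected, and nothing in the conflict favours one arm. It should be corrected, but it does not threaten the trial's main conclusion.

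**What to change.** Replace the sentence in section 5.1 with: *Haematology and clinical chemistry will be done at baseline and, for all patients, at every visit marked in the section 3.6 table, and additionally as clinically indicated. Urine analysis and pregnancy tests will be done as scheduled in that table and repeated only if clinically indicated.*

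The cost is one sentence, handled under the amendment procedure in section 7.7. The visits and panels are already in the schedule, and no urine or pregnancy test is added. If the sponsor did not in fact intend routine bloods after week 24, the table and text of section 3.6 should be changed instead for those visits. The week 8, 20 and 24 panels should stay unconditional in either case.
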